## Abstract

**Introduction:**

High-quality early childhood education can fundamentally alter children’s long-term education, earnings and well-being. In low-resourced settings, children’s development is hampered by undernutrition, poverty and limited access to services. This study will generate high-quality evidence on child development from children who both attend and do not attend daycare across informal settlements in Kenya by (1) examining the relationship between child development, nutritional status and household characteristics using a large, community-based sample and (2) measuring the impact of exposure to improvements in childcare quality on child development and nutritional status.

**Methods and analysis:**

We combine a cross-sectional observational study of child development and anthropometrics among approximately 4700 children aged 0–5 across 11 counties in Kenya with a cluster randomised controlled trial that measures the impact of improved daycare quality on these outcomes. We use International Development and Early Learning Assessment to measure child development and record child height and weight to measure height-for-age and weight-for-height z-scores. Primary analyses will (1) estimate associations between child development outcomes and nutritional status using multivariable regression models, adjusting for prespecified covariates; and (2) examine differences in outcomes between children attending daycares in communities exposed to quality improvements and children attending daycares in control communities. Subgroup analyses will examine heterogeneity by child sex and daycare participation.

**Ethics and dissemination:**

The Strathmore University Institutional Scientific and Ethical Review Committee (SU-ISERC) has provided ethical review for this study, with initial approval SU-ISERC1602/23. This study has also received IRB approval from The Ohio State University (#2023B0300). Written informed consent will be obtained from caregivers before participation. We will disseminate findings through peer-reviewed publications, policy briefs and presentations to local stakeholders, and we will publish de-identified data and replication code on a public repository.

**Trial registration number:**

AEARCTR-0011747.

STRENGTHS AND LIMITATIONS OF THIS STUDYWe use well-established methods and tools to measure nutritional status and early child development: we conduct direct anthropometric assessments using standardised field protocols, and we measure early child development outcomes using a validated, age-appropriate instrument (International Development and Early Learning Assessment) administered by trained enumerators.Data collection targets children aged 0–5 living in informal settlements across Kenya, a hard-to-reach population at high nutritional risk.Randomised assignment to differing levels of exposure to high-quality daycare provides a rigorous design to compare child outcomes while minimising confounding from provider and household characteristics.The sample is not randomly drawn from the informal settlements, and the sample of daycare users could not be recruited prior to randomisation due to high turnover in daycare enrolment.Due to the nature of the setting where measurements need to take place, collected data may be noisier, as some children who are being weighed may not be minimally dressed and the child development assessment may be conducted in a more crowded or distracting area than ideal.

## Introduction

### Background and rationale

 High-quality early childhood care and education is a determinant of children’s health, development and well-being, with strong evidence linking early environments to improved educational attainment, labour market outcomes and adult health.^1^,^3^ In many low-income and middle-income countries, including Kenya, such care remains scarce or unaffordable, especially for poor households.^4^,^7^ While Kenya substantially expanded public access to preprimary and primary school in recent years, families with young children rely heavily on the private market or informal arrangements for care.

In the urban informal settlements that house nearly half of Kenya’s urban population, paid daycare is largely informal and unregulated, with high child-to-caregiver ratios, limited caregiver training, few safe and stimulating materials, and insufficient opportunities for responsive and positive caregiver interactions.^8 9^ We find that 44% of daycares located in informal settlements across Kenya report having no toys and 37% have no books.^10^

Evidence from both high-income and low-income settings shows that structured and supportive interactions between caregivers and children are key pathways through which childcare quality influences developmental trajectories.^11^ Providers who are responsive, nurturing and cognitively stimulating promote secure attachment, language development and early learning skills,^12^ while low-quality childcare can constrain children’s socioemotional development and school readiness.^13^ Early childhood nutrition is also fundamental to child development, learning and future academic achievement.^14^ Malnutrition—whether due to insufficient calories, poor dietary diversity or micronutrient deficiencies—can impair brain development, reduce attentiveness and weaken immune function.^1 15^ In informal settlements in Kenya, approximately one-third of residents live below the poverty line, in conditions associated with malnutrition and micronutrient deficiencies.^16^ Roughly half of young children in Nairobi informal settlements are stunted,^17 18^ and we find that 40% of daycares report that at least one child spends the day hungry at least once per week.^10^ Informal daycare attendance may be associated with worse nutrition status,^19^ but this relationship may not be causal if malnutrition is correlated with enrolment decisions. Given this context, it is *a priori* unclear whether attending daycare is positively (or negatively) associated with health outcomes for children in informal settlements.

Although this population is highly vulnerable, data on child development and nutritional status in informal settlements are extremely limited. Families living in these settlements are mobile and hard to reach, making it particularly difficult to collect high-quality data.

We address this gap by (1) documenting child development and nutritional status for approximately 4700 young children in 51 informal settlements across Kenya and (2) assessing the causal impact of improvements in childcare quality on child development and anthropometric measurements for children enrolled in paid daycares within these settlements. A reliable, high-quality measurement of early childhood cognitive and physical development outcomes among a low-income population in Kenya is fundamental for policy design, as is an understanding of the effect of efforts to improve daycare services available to them on these outcomes.

In this study, we build on an existing cluster randomised controlled trial (C-RCT) that has been underway in informal settlements in Kenya since 2024 and involves nearly 1000 daycare firms.^10^ We will collect and analyse data on child development for children aged 3–5 (roughly 2700 children) and child anthropometric measurements for children aged 0–5 (roughly 4700 children) in the same communities where these daycares operate. The intervention within the C-RCT focuses on improving the quality of paid daycare, including improvements in caregiving practices, infrastructure and the provision of nutritious food. The study sample includes (a) young children from households enrolled in the study before the intervention and (b) young children currently enrolled in centres located in treatment and control communities.

### Study objectives

To measure early child development in children 3–5 living in informal settlements in Kenya through the International Development and Early Learning Assessment (IDELA) and compare our results to existing measurements of child development outcomes found elsewhere.To assess the prevalence and severity of nutritional status deficiencies for children aged 0–5 living in informal settlements across Kenya through anthropometric measurements.To determine the correlates of both early child development and nutritional status, including whether paid caregiving arrangements are associated with children’s outcomes.To measure the causal impact of improvements in childcare quality on early child development and anthropometric measurements of nutritional status.

## Methods: participants, interventions and outcomes

### Study background

The protocol described here builds on an ongoing C-RCT by (1) including a new sample of children enrolled in our study daycares and (2) collecting new data on anthropometric measurements and direct assessments of child development. The existing C-RCT measures the impact of a social franchising model designed to improve childcare quality on firms and families.^10^ We partnered with a Kenya-based social franchising organisation that supports and facilitates the improvement of existing daycare centres through training and continuous mentorship on various areas relevant to running a daycare, including high-quality caregiving practices, health and safety, and business management. The intervention also includes a facility improvement grant and is broad, with components that could improve child health and nutritional status both directly and indirectly. First, the organisation requires and supports improved sanitation practices (eg, installing wash stations, separating toileting from eating locations, etc). Second, it works to improve the physical infrastructure, such as providing rugs for floors. Third, it provides subsidised, fortified porridge for children. These intervention components may directly improve nutritional status and increase cognitive development of children through improved engagement and nutrition.

For the C-RCT, we randomly assigned 25 communities to receive the treatment and 26 to be in the control group, stratifying by county. The research team conducted this randomisation independently after the firm listing, firm baseline and household listing were complete, at which point it shared the assignment with the implementing partner. In treatment communities, the social franchising organisation offered its programme to all existing daycare firms, and it trained and enrolled those interested in its services. The organisation did not enter control communities, allowing us to compare impacts in areas with and without exposure to the franchising model. In this study,^10^ we measure the impact of this social franchising model on childcare quality, provider revenues and parental work outcomes in urban informal settlements across Kenya.

In this protocol, we outline the procedures and expected contribution of the proposed study, which builds on this existing C-RCT. The overall study timeline is shown in figure 1, and the Consolidated Standards of Reporting Trials Statement (CONSORT) diagram is shown in figure 2. For this addition, we recruit children currently enrolled in daycare centres in both treatment and control communities, but who may not have been in our original study sample (as the sample frame for children in the latter comes from the community and will include both children who participate in daycare and those who do not). The current study focuses on children—rather than daycare firms or households—to measure child development and nutritional status among children who do and do not attend daycare in the study communities, and it compares outcomes between treatment and control communities.

**Figure 1 F1:**
[figure not shown]
Study timeline. The figure shows timing for firm and household listing and baseline, randomisation and intervention, and two phases of child assessment. C-RCT, cluster randomised controlled trial. T&C, treatment and control.

**Figure 2 F2:**
[figure not shown]
CONSORT diagram. The figure shows the selection and randomisation of communities, along with planned child recruitment from both the baseline sample and workshop daycares. CONSORT, Consolidated Standards of Reporting Trials Statement; IDELA, International Development and Early Learning Assessment.

### Study setting

We conduct our study in 51 low-income urban informal settlements located across 11 counties in Kenya. In early 2024, we first carried out an exercise to define the boundaries of the study communities, and therefore potential daycares and children living within them. With guidance from local leaders, study team members walked around the communities and outlined polygons using GPS that would correspond to cluster boundaries for each community. The boundary area was designed to be large enough to include a minimum number of eligible daycares; mapped boundaries were then adjusted accordingly to ensure that each community had at least 10 operating daycares.

### Firm recruitment

Within the 51 communities, we conducted a census of all paid daycares, and then a baseline survey with a subset in early 2024, reaching 978 providers. Our implementation partner then invited surveyed firms in treatment and control communities to attend a free half-day child development workshop. We denote the roughly 60% of baseline firms that attended this workshop as the ‘workshop sample’ (see Fitzpatrick *et al*^10^ for more details on their characteristics). In treatment communities, 82.5% of the workshop sample then opted to continue the partner’s programme, undergoing quality improvements and further training. Workshop-attending firms are comparable between treatment and control communities across the range of characteristics we consider, thus allowing us to use the ‘workshop sample’ to compare children in daycares that joined the social franchising organisation in treatment communities with children in daycares that would have likely joined the programme if the implementation partner had entered their community.

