### Data analysis

First, we will analyse and produce descriptive statistics of the key child development outcomes listed above. Second, we will compare these measurements for children in the treatment communities to those in control communities according to the larger study’s randomised design using multivariable regression. We will include controls for child age, sex and strata (county) fixed effects.

We will also examine these outcomes separately for the C-RCT baseline sample and daycare user sample. Because C-RCT baseline households were identified prior to randomisation and the intervention, we anticipate that differences in outcomes will reflect the causal intention-to-treat impact of improved childcare in the community. For the daycare user sample, we will capture the treatment-on-treated effect, but this could be biased if the quality improvement affected the selection of children into daycares.

We will restrict our child development analysis to children for whom we obtain IDELA data. Furthermore, we restrict our nutritional status analysis to children for whom we obtain valid anthropometric measurements. In the event of missing independent variables, we will code them as zero and include a missing variable flag.

Cross-sectional data gathered concurrently through caregiver and daycare firm surveys will produce a large dataset for measuring the relationship between early child development and nutritional status, as well as whether paid caregiving arrangements are associated with children’s health and development outcomes.

The final report of this study will follow the general CONSORT.

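### The daycare user comparison rests on firms that chose to attend a workshop whose timing relative to allocation is not stated; measured balance cannot exclude firm selection by arm, and the listed model has no firm covariate

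*Protocol article*

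**What the plan says.** All references are to the protocol article.

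- **Study background.** On allocation: "we randomly assigned 25 communities to receive the treatment and 26 to be in the control group, stratifying by county". On timing: "The research team conducted this randomisation independently after the firm listing, firm baseline and household listing were complete", and "at which point it shared the assignment with the implementing partner". The same section says that the franchising organisation stayed out of control communities.
- **Firm recruitment.** The firm baseline in early 2024 reached 978 providers. Next: "Our implementation partner then invited surveyed firms in treatment and control communities to attend a free half-day child development workshop". Roughly 60% attended and form the workshop sample; the rate is not split by arm. Of the treatment attenders, 82.5% went on to the programme. The section then asserts: "Workshop-attending firms are comparable between treatment and control communities across the range of characteristics we consider, thus allowing us to use the ‘workshop sample". The purpose is to set children in treatment daycares that joined against children in control daycares thought likely to have joined had the partner been there.
- **Figure 2 caption.** Workshop daycares are the second source of children, beside the baseline sample.
- **Data analysis.** "We will include controls for child age, sex and strata (county) fixed effects". The daycare user estimate is called a treatment-on-treated effect, with one caveat: "but this could be biased if the quality improvement affected the selection of children into daycares".

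**The concern.** Membership of the daycare user sample depends on a choice made by each provider. If that choice came after allocation, and invitations came from a party that held the allocation, the kind of firm that attended could differ between arms. In treatment communities the workshop led on to training and a facility improvement grant; in control communities it led to nothing further. Balance on measured characteristics cannot show balance on motivation or on unmeasured quality.

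Such selection would act on firms, so it would remain even if no family changed daycare. The caveat about children's selection into daycares therefore does not cover it. Nor would the listed controls remove it, since none describes the firm, although baseline firm data exist. At stake is how far the daycare user contrast can be read as the effect of the programme rather than of which providers entered the sample.

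**Working it through.** **1. Order of events.** Study background gives: firm baseline, then randomisation, then disclosure to the partner. Firm recruitment gives: firm baseline, then workshop. Neither orders the workshop against randomisation. Two sequences fit:

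- *Baseline, randomisation, workshop.* Describing invitees by arm, and treatment attenders moving on to the programme, make this plausible. Attendance is then a post-allocation choice.
- *Baseline, workshop, randomisation.* The arm labels could be retrospective. Attendance is then a pre-allocation trait, protected by randomisation.

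Figure 1, the timeline, is not visible in the text available here and may settle this.

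**2. When attendance biases the contrast.** Suppose firms attend when a latent trait exceeds a threshold. Among attenders at rate p the trait has mean λ(p) = φ(z₁₋ₚ)/p. With s the firm-level component of the child outcome linked to the trait, bias = s × [λ(p_T) − λ(p_C)]. The rates by arm and s = 0.1 to 0.4 SD are assumptions.

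- 60% v 60%, same mechanism: bias = 0.
- 65% v 55%: λ = 0.570 and 0.720, difference −0.150, so 0.015 to 0.060 SD in size.
- 70% v 50%: 0.030 to 0.121 SD in size.

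The sign depends on how the trait relates to child outcomes. Equal rates do not exclude bias if different types of firm attended.

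**3. Worst case by trimming.** For attendance a v b, the excess fraction is q = (a − b)/a and the largest shift in the mean is SD × φ(z_q)/(1 − q). For an assumed daycare-level SD of 0.3 to 0.4:

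- 62% v 58%: q = 0.04/0.62 = 0.065; shift 0.040 to 0.054 SD.
- 65% v 55%: q = 0.10/0.65 = 0.154; shift 0.084 to 0.112 SD.

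This bound takes the excess firms to be exactly the most extreme on the outcome.

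**4. Joiners against all attenders.** Attenders number about 0.60 × 978 = 587. If they split 25:26 by arm (assumed), about 288 are treatment firms, of which 0.825 × 288 ≈ 237 joined. If treatment is limited to joiners while control keeps every attender, bias = (1 − 0.825) × d = 0.175d, where d is the outcome difference between joiners and non-joiners without the programme: 0.044 SD at d = 0.25 and 0.0875 SD at d = 0.5. The article gives no value for d.

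**5. Scale.** The article states detectable effects of 0.14 SD (anthropometry) and 0.25 SD (child development), taken here at face value. At 65% v 55% the threshold model gives 0.015/0.14 = 11% to 0.060/0.14 = 43% of the first. The worst case gives 0.112/0.14 = 80% of the first and 0.112/0.25 = 45% of the second.

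**The case against.** A reader might infer that the arms of the daycare sample are themselves self-selected. The documents do not support that. Arms were set by randomising 51 communities, and firms in both arms were invited to the same free half-day event. A filter common to both arms limits generalisability and does not by itself bias the contrast. Offering the workshop in both arms is also a sensible device for finding likely joiners among control firms.

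A reader might also take it as established that the workshop came after randomisation, or that firms knew a grant would follow only in treatment communities. The article says neither. It does not say what firms were told when invited, and the partner holding the allocation does not show that providers knew it.

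The article further reports balance between workshop firms and points to the main trial paper for their characteristics. A separate analysis plan may add covariates. The article already warns that the daycare user estimate could be biased, and it keeps the causal intention-to-treat reading for the baseline sample.

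Most of this stands, and it limits the point to a possible bias of unknown size. It does not repair the step from balance on the characteristics considered to a valid comparison, or the caveat that names children's selection only. An unseen plan may well hold more covariates; the point here is that the stated model would be better with firm baseline data in it.

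**Conclusion.** The point holds in a limited form. The daycare user sample passes through a voluntary firm-level step that may have followed allocation. The order is not stated, and measured balance cannot exclude a difference by arm. A second selection enters if treatment firms that did not join are dropped. The article's framing as joiners, and its treatment-on-treated label, make that possible without stating it.

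No bias is demonstrated. If attendance preceded randomisation, or did not differ by arm in rate or type of firm, the attendance step contributes none. The figures of 0.015 to 0.06 SD (threshold model, 65% v 55%) and up to about 0.11 SD (worst case) rest wholly on assumed attendance rates and firm-level variation. They show that a modest difference could matter beside the stated detectable effects; they are not estimates. The change is worth making because it costs little and the baseline firm data are already in hand.

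**What to change.** 1. In the daycare user analysis, compare all workshop daycares by assigned arm. Add a short, prespecified set of firm baseline characteristics already collected to the child age, sex and county controls. If the selected treatment daycares are joiners only, say so.
2. In Study background and Firm recruitment, state whether workshop invitations came before or after the allocation was disclosed. Reconcile the statement that the organisation stayed out of control communities with its invitations to control firms.
3. If invitations came after disclosure, name firm selection beside child selection in Data analysis and report attendance by arm. If attendance differs, give trimming bounds as a sensitivity analysis.

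The cost is a few degrees of freedom, some wording and a more cautious claim for this sample. Comparing all attenders also dilutes the effect: if non-joining firms gain nothing and the 82.5% uptake holds in the sampled daycares, the contrast estimates about 0.825 of the effect in joiners.
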